### Study aims and objectives

The primary objective of this trial is to interrupt the transmission of LF with a twice-yearly treatment with IVM and ALB. The secondary objectives are to assess the impact of the twice-yearly treatment on transmission of parasite in areas of persistent transmission and evaluate the cost-effectiveness of a twice-yearly treatment versus the current yearly treatment based on IVM and ALB. The study will also include process and economic evaluations to assess the feasibility and implementation of the twice-yearly treatment, which will guide scale-up similar interventions in other settings in Africa. The more detailed study objectives are:To quantify the impact of twice-yearly versus yearly community treatment (treatment strategies and delivery systems) in reducing parasitological and entomological LF transmission indices in ‘hotspot’ areasTo evaluate the costs and cost-effectiveness of twice-yearly treatment in reducing LF transmissionTo assess the extent to which the twice-yearly treatment is acceptable to the community and feasible, given the health system capacity, and can be easily scaled-up elsewhereTo assess the impact of IVM and ALB treatment on other intestinal and soil-transmitted helminthes (STH)

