### Treatment interventions

All study groups will receive treatment with 400 μg/kg IVM + 400 mg ALB, which is highly efficacious against *W. bancrofti* [1]. The difference between the study groups is the frequency of treatment provided (Table 3). The MDA will be implemented in all communities as part of the ongoing NTDP. In Ghana, MDA started in the year 2000 as part of the GPELF. Treatment with 400 μg/kg IVM + 400 mg ALB is provided annually by trained CDDs. Every year, the national team organises training for regional, district, subdistrict supervisors, CDDs and their supervisors. They are also taken through their roles and responsibilities. The programme targets all eligible individuals aged 5 years and above in all endemic districts and communities. The strategies follow the door-to-door Directly Observed Treatment (DOT) strategy [35]. This study will follow the exact MDA strategy used by the NTDP and no modifications other than the frequency of treatment will be made. All treatments will be undertaken through the systems established by the NTDP. Further, the onchocerciasis programme in Ghana undertakes twice-yearly treatment with IVM in hyperendemic areas, and the twice-yearly treatment in LF-endemic areas will be an extension of the onchocerciasis program.

**Table 3 Tab3:** Drug dosage and schedule

Arms	Assigned interventions
Control group	400 μg/kg ivermectin + 400 mg albendazole tablets given every year for 2 years
Expanded frequency group	400 μg/kg ivermectin + 400 mg albendazole tablets given every 6 months for 2 years

Routinely, treatment by the NTDP is done from house to house. CDDs also visit schools to treat after prior notification. Treatment is also done at the markets and sometimes at the church and mosque. Work in the districts is monitored and supervised by coordinators. The team supervisors supervise five or six teams, each of which is made up of two CDDs. Communities are demarcated into sections and marked according to days they are to be visited. Teams under a supervisor work in demarked sections in a ‘sweeping’ fashion one after the other each day (i.e. the whole group move to a section, finish the work there and move to the next). The last day is used to ‘mop up’ though all the sections of the area to which the group has been allocated.

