### Entomologic surveillance

Surveys for vectors and transmission of LF will be carried out quarterly throughout the first year, and subsequently every 6 months. Vector collection will be carried out in selected villages. To ensure that mosquitoes do not cross over between communities, vector collection communities will be at least 2 km apart.

In each community collections will be undertaken in 10 selected participants’ households, distributed so as to be representative of the community. The community will be divided into four approximate sections. All households in the section will be numbered. The day before the planned collection, the dice will be rolled to select the households. For example, if the dice is rolled and the number is 5, then the fifth house will be selected. Upon selection, the household head will be approached, the study explained and consent sought. If a household refuses participation or household members are absent, a different household will be selected as a replacement. Subsequently, the sum of the dice rolls will be added to the previous number, for the selection of the remaining households. At least two households will be selected per section.

Collections will be undertaken using the Pyrethrum Spray Collection (PSC) in the rooms provided by the consenting individuals. The PSC will be undertaken in the morning from 5 a.m. to 8 a.m. White bed sheets will be laid on the floor and other surfaces in the rooms, after mosquito hiding places (under the bed, tables) have been disturbed to displace any resting mosquitoes. The room will then be sprayed with pyrethrum insecticide (RAID insecticide), commonly found on the Ghanaian market) and left for about 15 min, after which the white sheets will be inspected for any dead or knocked down mosquitoes. The mosquitoes will be collected and placed in a petri-dish labelled with the village name, GPS coordinates and collection date. Collected mosquitoes will be identified using morphological identification keys [36, 37]. All mosquito collections will be undertaken by trained entomologists at the NMIMR.

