### Data management and analysis

Field and laboratory data will be recorded by technicians using Samsung Galaxy Tabs A7.0., and entered into a customised database. All data collections tools are coded using CSPro and the data will be transferred onto a secured server.

The analysis will be aimed at (1) assessment of any differences in baseline characteristics between treatment groups, (2) intent-to-treat analysis, i.e. assessment of the effectiveness of the single or twice-yearly treatment regimens on infection intensities and disease outcome and (3) assessment of differences in adherence to the treatment regimens between the groups, potential confounding, and adjusted effectiveness analysis.

All statistical analyses will be based on the clusters with both baseline and endpoint parasitological results. Results will be presented as appropriate effects sizes with a measure of precision (95% CIs). Unadjusted and adjusted results will be presented for all analyses. Covariates in adjusted analyses will be predefined and will include participation in previous MDAs and access and use of bed nets. For continuous outcomes, analyses will adjust for baseline by inclusion of the cluster mean of the outcome in question as a covariate in statistical models.

Demographic and population characteristics of clusters will be compared between study groups. These measures will be tabulated, but no significance tests will be performed to investigate for differences between groups at baseline. Statistical testing will be restricted to comparison between the two community-based treatment groups. Secondary outcomes will be pre-specified for statistical testing along with the primary outcome.

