The summary statistic for each parasitological endpoint will be estimated, and compared using paired Student’s *t* tests. Changes in rate of infection will be expressed as percentage differences from the pre-treatment rates. The significance in differences in mosquito infection rates will be tested using the chi-square test. The significance of correlation between different indices will also be tested using the chi-square test. The significance of differences in monthly transmission potential before and after treatment will be tested with the non-parametric Mann-Whitney *U* test. Analysis of variance (ANOVA) will also be used in the intent-to-treat analysis for comparing the study groups. SPSS for WINDOWS 16 (SPSS Inc, Chicago, IL, USA) will be used for all statistical computations. The mf intensities will be adjusted for sampling time by multiplying the counts with a time-specific factor [38]. Geometric mean intensities (GMIs) of microfilaraemia and antigenaemia prevalence will be calculated [39].

Below is the statistical analysis strategy.

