#### Analysis strategy

Each of our study outcomes, i.e. prevalence and intensity of *W. bancrofti* mf, will be considered separately during the analysis. Loss to follow-up was taken into consideration during our sample size calculation. Therefore, regardless of the number of incomplete observations, we expect to end up with no less than 58 complete observations per community at the end of the study.

A panel of individual line plots for the study participants would be used in the assessment of within-person variability. Since the assumptions of likelihood are violated by the effect of within-group and within-subject clusters in longitudinal data, in assessing the transmission dynamics of LF infection, the measured covariates will be regressed separately on both the prevalence and the intensity of infections using a quasi-likelihood method, i.e. generalised estimating equations, which uses an association matrix instead of the diagonal matrix employed by the generalised linear models. As part of the model validation, the point-referenced residuals of the provisional models will be assessed for spatial autocorrelation. The results of this assessment would help to determine if unmeasured/unobserved factors in the study areas play relevant roles in the transmission dynamics of LF infections. Using classical geostatistical concepts, our final model would be adjusted for both the effects of the measured and unobserved factors.

For entomological endpoints, infection rates will be determined, using the polymerase chain reaction (PCR) [40] and LAMP [41] methods. The results will be analysed using the poolscreening software by Katholi and colleagues [42, 43].

The findings and data from this study will be used to develop a mechanistic model, which describes the variability in treatment responses in populations. This will be implemented into an already available and well-established transmission dynamic model for LF (LYMFASIM) [44, 45], which will then be used to systematically explore the consequence of twice-yearly treatment on the long-term impact of MDA and elimination prospects. LYMFASIM simulates the spread of *W. bancrofti* in a human community and the impact of control measures, with the advantage of accounting for a variety of parameters specific to the population of interest and output predictions [45, 46].

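### The planned test of monthly transmission potential compares before with after treatment when every cluster is treated, so it does not address twice-yearly versus yearly and conflicts with the protocol's own between-arm rule

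*Protocol article*

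**What the plan says.** All statements are in the protocol article.

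- **Objective** (Study aims and objectives): "To quantify the impact of twice-yearly versus yearly community treatment (treatment strategies and delivery systems) in reducing parasitological and entomological LF transmission indices" in hotspot areas.
- **Treatment** (Treatment interventions): all study groups are treated, and "The difference between the study groups is the frequency of treatment provided".
- **Testing rule** (Data management and analysis): "Statistical testing will be restricted to comparison between the two community-based treatment groups". The same section adjusts continuous outcomes for the cluster mean at baseline and promises effect sizes with 95% confidence intervals.
- **Transmission potential** (same section): "The significance of differences in monthly transmission potential before and after treatment will be tested with the non-parametric Mann-Whitney" U test. No comparison of arms is named for this index.
- **Mosquito infection** (same section): "The significance in differences in mosquito infection rates will be tested using the chi-square test", without saying what is compared with what. The Analysis strategy under Secondary outcomes adds, for entomological infection rates: "The results will be analysed using the poolscreening software".
- **Schedule** (Entomologic surveillance): "Surveys for vectors and transmission of LF will be carried out quarterly throughout the first year, and subsequently every 6 months". Collections are made in selected villages. The number per arm is not given.

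**The concern.** The randomised question is whether a second yearly round lowers transmission more than one round does. A before/after contrast answers another question: whether the index changed over time in villages that were all treated. Any effect of MDA common to both arms, and any time trend unrelated to treatment, goes into that contrast. A significant fall could then be read as support for twice-yearly treatment although the same fall occurred under annual treatment.

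The choice of test is a second, smaller problem. Mann-Whitney is for two independent samples. If the same villages are visited before and after, the two sets of values are paired.

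This matters because the Background presents the lack of vector data as a gap in earlier trials, and the Discussion promises to determine the effect of frequency on entomological indices.

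**Working it through.** The article gives no entomological sample size, power or effect, so there is no stated figure to reproduce. The check has three parts.

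**1. What each contrast estimates.** Let the mean change in log transmission potential be δ₁ in the annual arm and δ₂ in the twice-yearly arm, with equal numbers of villages.

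- Before/after, arms pooled: (δ₁ + δ₂)/2.
- Randomised comparison: δ₂ − δ₁.

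If frequency has no effect, δ₁ = δ₂ = δ. The first quantity is δ and the second is 0. The before/after test then rejects at its power to detect δ, not at 5%. Run within one arm, it estimates δ₁ or δ₂ alone, which is still not the difference.

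**2. Illustration.** These inputs are assumptions, not figures from the article: 9 villages per arm (all clusters, so the most possible); one normally distributed log value per village before and after; total SD 1; within-village correlation ρ of 0, 0.5 or 0.8; the same decline d in both arms; two-sided 5% level; 4,000 simulated trials per setting. The before/after tests pool all 18 villages. Entries are the percentage of runs that reject.

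| d (SD) | ρ | Mann-Whitney, before/after | Signed-rank, before/after | Mann-Whitney on village change, between arms |
|---|---|---|---|---|
| 0 | 0 | 5.4 | 5.3 | 4.4 |
| 0 | 0.5 | 1.0 | 5.4 | 4.2 |
| 0 | 0.8 | 0.05 | 4.9 | 3.7 |
| 0.5 | 0 | 30 | 29 | 4.5 |
| 0.5 | 0.5 | 22 | 47 | 4.1 |
| 0.5 | 0.8 | 16 | 86 | 3.8 |
| 1.0 | 0 | 80 | 78 | 4.0 |
| 1.0 | 0.5 | 88 | 97 | 4.0 |
| 1.0 | 0.8 | 94 | 100 | 3.5 |

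In every row the true difference between arms is zero. The between-arm test stays at or below 5%. The before/after tests follow the common decline.

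**3. Direction of the pairing error.** With n villages, the variance of the mean change is 2σ²(1 − ρ)/n. An independent-samples analysis in effect uses 2σ²/n. The ratio of true to assumed variance is 1 − ρ, so 0.5 at ρ = 0.5 and 0.2 at ρ = 0.8. The assumed variance is too large and the test too cautious. The table agrees: with no change, rejection falls to 1.0% and 0.05%; at a 0.5-SD decline and ρ = 0.8, Mann-Whitney detects 16% where a paired test detects 86%.

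**The case against.** The best defence is that the plan as a whole does compare arms. The between-arm rule is general, and the baseline-adjustment sentence covers continuous outcomes without limiting them to parasitology. ANOVA is also planned for comparing the study groups. The article is condensed, and an analysis plan may say more. This shows what was probably intended, but it does not remove the conflict: one sentence fixes a different contrast and test for a named index. The ANOVA belongs to an intent-to-treat analysis that the article describes by infection intensities and disease outcome, with no entomological index named.

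Several stronger readings are tempting, and the article does not support them:

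- **That all entomological tests are before/after.** Only the transmission-potential sentence is. The chi-square for infection rates has no stated contrast and, under the general rule, could well be between arms.
- **That the chi-square needs the status of each mosquito, or ignores villages.** It could be run on counts of positive pools, and the unit is not stated. What stands is that it is not linked to the pool-screening.
- **That season confounds the comparison.** The rounds that count as before and after are not named, and six-monthly rounds can fall in the same months as first-year rounds. It is a risk, not an established fault.
- **That the arms would be tested separately and compared on significance.** The article does not say so, and any rate of disagreement would rest on an invented power.
- **That ignoring the pairing creates false positives.** With positive correlation it does the opposite. Because households are drawn by dice before a collection, pairing is also weaker at household level than at village level.

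**Conclusion.** The point holds for monthly transmission potential. The stated contrast does not estimate the effect of treatment frequency, and it contradicts the testing rule and the baseline-adjustment approach in the same section. A significant fall is to be expected whenever MDA lowers the index, whether or not frequency matters.

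The percentages in the table illustrate this and do not predict this trial's results. In villages that have already had 13 to 15 yearly rounds, the common decline may be smaller than the 1 SD used in the last three rows. The loss of power from the unpaired test depends on the same villages being revisited, which the article implies but does not state.

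The weight is moderate. Table 2 lists no entomological index among its outcomes, so the primary result is untouched. But the index serves the first detailed objective, and the correction is easy while the data are still being collected.

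**What to change.** - **Transmission potential.** Replace the sentence with a between-arm comparison of village-level values at matched survey rounds, with the village as the unit. Use either change from the first round or the follow-up value adjusted for the village's baseline, as the section already does for continuous outcomes. Give the estimate and its 95% interval. Report before/after changes descriptively, without a test.
- **Mosquito infection rates.** State that the contrast is between arms, and base it on the pool-screening estimates with allowance for village.
- **Rewording the rule is not enough.** Allowing before/after tests would remove the contradiction but still leave the objective without a named test for this index.

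**Cost.** The change is to the analysis text and needs no new data for the villages already planned. Intervals will be wider because villages carry the comparison. Power may be low, since the number of collection villages per arm is not given. With an assumed three per arm there are C(6,3) = 20 allocations, so the smallest two-sided permutation p-value is 2/20 = 0.10 and significance at 5% is out of reach. With four per arm it is 2/70 = 0.029. The number should be stated. If it is small, the result should be given as an estimate with its interval and not rest on a test.

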## Primary outcome: prevalence of LF infection measured at 12, 24 and 30 months post intervention

### Testing the study hypothesis

The additional treatment that will be administered to the intervention group, 6 months after the national mass drug administration (MDA) for 2 consecutive years, will constitute the main intervention in this study. The effect of the intervention will then be assessed by measuring our primary study outcome in both the control and intervention groups at 12, 24 and 30 months. Therefore, our study hypothesis will be tested by comparing the rates of the primary study outcome in the intervention and control groups over time.

#### Pre-post analysis

Since the emphasis is on the comparison of the intervention and control groups, each of the follow-up measurements will be analysed in relation to the baseline measurements of the outcome in a pre-post analysis. For instance, Y_i0_ = 1 to Y_i1_ = 0 in Eq. 1 would indicate a favourable effect of the intervention in group 2 while Y_i0_ = 1 to Y_i1_ = 1 would indicate no effect and Y_i0_ = 0 to Y_i1_ = 0 will be considered a preventive effect:1$$ \left\{\begin{array}{l}{Y}_{\mathrm{i}0}=1\to {Y}_{\mathrm{i}1}=0\hfill \\ {}{Y}_{\mathrm{i}0}=0\to {Y}_{\mathrm{i}1}=1\hfill \\ {}{Y}_{\mathrm{i}0}=0\to {Y}_{\mathrm{i}1}=0;\kern1em {Y}_{\mathrm{i}0}=1\to {Y}_{\mathrm{i}1}=1\hfill \end{array}\right., $$

where the baseline measurement of the outcome for the i^th^ participant is given by Y_i0_;

Y_i1_ denotes the measured outcome at the first follow-up; and 1, 0 indicate the presence or absence of LF infections, respectively.

Therefore, by subsetting on each of the possible scenarios of the baseline measurements (Eq. 2), the control and intervention groups could be compared using second-order transition models where separate logistic regression models will be fitted for each of the possible scenarios:2$$ \left[\begin{array}{ll}\upchi 00\hfill & \upchi 01\hfill \\ {}\upchi 10\hfill & \upchi 11\hfill \end{array}\right], $$

where χ_00_ is the probability that the follow-up measure of the outcome and Y_ij_, is 0 when the baseline measurement is also 0.

Results will be presented separately for every time point and then after the study, the overall effect of the intervention will be analysed, taking all time points into consideration. Further, after the first time point we would employ a generalised linear mixed model to account for the correlation between the repeated measurements per individual.

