**Methods:**

A cluster randomised trial will be implemented in LF-endemic communities in Ghana. The interventions will be yearly or twice-yearly MDA delivered to entire endemic communities. Allocation to study group will be by clusters identified using the prevalence of LF. Clusters will be randomised to one of two groups: receiving either (1) annual treatment with IVM + ALB or (2) annual MDA with IVM + ALB, followed by an additional MDA 6 months later. The primary outcome measure is the prevalence of LF infection, assessed by four cross-sectional surveys. Entomological assessments will also be undertaken to evaluate the transmission intensity of the disease in the study clusters. Costs and cost-effectiveness will be evaluated. Among a random subsample of participants, microfilaria prevalence will be assessed longitudinally. A nested process evaluation, using semi-structured interviews, focus group discussions and a stakeholder analysis, will investigate the community acceptability, feasibility and scale-up of each delivery system.

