### Study outcomes and measurements

The primary outcome, the prevalence of LF infection, will be measured through cross-sectional parasitological surveys conducted at baseline and at 12, 24 and 30 months’ follow-ups. Figure 1 presents a flowchart of the study design. The timing of the final follow-up survey will take into account differences in time since treatment of the annual and biannual treatment groups at 24 months. The time point assessments at 12, 24 and 30 months will allow us to evaluate changes in the primary study outcome in the intervention and control groups over time. For secondary outcomes, a subsample of individuals from the clusters in each of the study groups will be followed longitudinally for 2.5 years in order to better understand the transmission dynamics of LF and to estimate key parameters for mathematical modelling of transmission dynamics and treatment impact. The impact of treatment on other STHs (roundworm (*Ascaris lumbricoides*), whipworm (*Trichuris trichiura)*, and the hookworms (*Ancylostoma duodenale* and *Necator americanus*) and any other species identified) will also be assessed. A nested process evaluation, using semi-structured interviews, focus group discussions (FGDs) and a stakeholder analysis, will investigate the community acceptability, feasibility and participation in the twice-yearly drug administration. The local and regional health system structures and processes will be evaluated to determine the feasibility to scale-up the interventions.

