### Longitudinal surveys

Individuals who are positive for LF antigen and microfilaria (at baseline) will be followed longitudinally to help quantify the transmission dynamics of LF. They will be asked to provide blood samples 1 month following treatment. Two milliliters of venous blood will be collected in heparinised capillary tubes at night between 9 p.m. and 2 a.m. The collected samples will be transported to the laboratory and analysed. Subsequently, they will be revisited at 3, 6, 9 and 12 months post treatment and asked to provide a sample, which will be examined for the presence of *W. bancrofti* mf [21, 22]. They will also be requested to provide stool samples for the examination of STH infections.

The study team will also conduct household visits to assess the extent of non-compliance to treatment and factors associated with non-compliance [28–33]. The assessment of non-compliance will be based on short, standardised questions, as well as a review of the community drug distribution register.

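### The primary outcome is prevalence from cross-sectional surveys, but the primary analysis models each person's change from baseline and does not target that prevalence

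*Protocol article*

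**What the plan says.** The Abstract (Methods) states: "The primary outcome measure is the prevalence of LF infection, assessed by four cross-sectional surveys". Study outcomes and measurements repeats that the outcome "will be measured through cross-sectional parasitological surveys conducted at baseline and at 12, 24 and 30 months". Table 2 registers the primary outcome as change from baseline prevalence at 12, 24 and 30 months. The section on testing the study hypothesis says that the hypothesis is tested by comparing the rates of this outcome between the two groups over time.

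The Pre-post analysis section then defines the analysis on individuals: "where the baseline measurement of the outcome for the i^th^ participant is given by Y_i0", with a second value for the same person at follow-up. The groups are compared "by subsetting on each of the possible scenarios of the baseline measurements", with a separate logistic model for each. A generalised linear mixed model for repeated measurements within a person follows, and an overall effect over all time points is to be analysed at the end. A person uninfected at both surveys "will be considered a preventive effect".

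Longitudinal follow-up is described elsewhere as a separate, secondary component. The Abstract says "Among a random subsample of participants, microfilaria prevalence will be assessed longitudinally". Longitudinal surveys says "Individuals who are positive for LF antigen and microfilaria (at baseline) will be followed longitudinally". Secondary outcomes describes 80 individuals from low, medium and high prevalence clusters, followed for 2.5 years.

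**The concern.** A transition from baseline to follow-up status exists only for a person examined on both occasions. Surveys called cross-sectional do not guarantee that. The text therefore leaves open whether the data for the stated primary analysis will exist.

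A second problem remains if the same people are seen again. Splitting by baseline status replaces one question (does twice-yearly treatment lower prevalence in the community?) with two (do more infected people clear, and do fewer uninfected people become infected?). The plan does not say how the two answers combine into a test of the null hypothesis in the Sample size calculation section. At stake is whether the primary hypothesis has one test that matches its outcome.

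**Working it through.** **Step 1. The sections side by side.**
- Redrawn samples: the Abstract and Study outcomes and measurements call the surveys cross-sectional and place longitudinal follow-up in a subsample.
- Same people: Sample size calculation allows for loss to follow-up and re-contacts participants 14 and 7 days before follow-up. Pre-post analysis models repeated measurements per person. The secondary analysis strategy expects at least 58 complete observations per community.
- No sentence says whether the later surveys draw new households or return to the baseline sample.

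**Step 2. If households are redrawn.** Participants have no planned baseline value of their own, so neither the transition models nor the per-person mixed model can be fitted as written. The longitudinal components do not fill the gap. Longitudinal surveys takes baseline positives only, with visits up to 12 months after treatment. Secondary outcomes describes a subsample not limited to positives, but presents it as secondary. Neither supplies the primary data for 18 villages at 12, 24 and 30 months.

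**Step 3. If the same people are revisited.** Let p0 be baseline prevalence, c the proportion of infected people who clear, and i the proportion of uninfected people who become infected. Then

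prevalence at follow-up = p0 × (1 − c) + (1 − p0) × i.

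The split models compare c and i between arms separately; the stated outcome is the weighted sum. At p0 = 4.6%, a one-point change in c moves prevalence by 0.046 points, and a one-point change in i moves it by 0.954 points. At p0 = 13% the weights are 0.13 and 0.87. Neither model alone answers the prevalence question. Two strata at three time points give 2 × 3 = 6 arm comparisons. The overall analysis and the mixed model are mentioned, but neither is made the test of the null hypothesis.

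**Step 4. Size of the strata in a cohort.** Inputs: 58 completers per village, inflated to 80, 18 villages, and prevalence 1% to 18.2% (Sample size calculation); nine clusters per arm (Cluster randomisation); 4.6% mf and 13% antigen prevalence in an earlier study (Background).

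The plan's own steps reproduce: 58 × 1.37 = 79.5, rounded to 80, and 18 × 80 = 1440. The 58 is taken as stated. It cannot be re-derived because the article gives no intracluster correlation.

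Infected per village = 58 × p; infected per arm = 9 × 58 × p; uninfected per village = 58 × (1 − p).

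| Baseline prevalence | Infected per village | Infected per arm | Uninfected per village |
|---|---|---|---|
| 1% | 0.6 | 5 | 57.4 |
| 4.6% | 2.7 | 24 | 55.3 |
| 13% | 7.5 | 68 | 50.5 |
| 18.2% | 10.6 | 95 | 47.4 |

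At 1% prevalence, the chance that a village has no infected completer is 0.99^58 = 0.56. If all 80 were seen, the middle rows would be 3.7 and 10.4 per village. If 37% of the 80 were lost, 80 × 0.63 = 50.4 would remain, giving 2.3 and 6.6.

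**Step 5. Reading single transitions.** With no treatment effect, and with status at the two surveys taken as independent (an assumption), the share uninfected twice is (1 − p)²: 0.954² = 0.91 at 4.6% and 0.87² = 0.76 at 13%, in both arms. Positive correlation within persons raises these shares. Clearance is also expected in both arms, because controls are treated too: Table 1 of the article shows mf positives falling from 17/48 to 4/48 three months after treatment. A single transition therefore says nothing about the added round; only a difference between arms does.

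**The case against.** A reader might infer that the primary models cannot be fitted at all. The document does not support that. The passages on loss to follow-up, re-contact and complete observations point to re-examination of the same people, in which case the models can be run. What stands is the contradiction.

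A reader might also infer that the only cohort consists of baseline positives, so that no transitions from uninfected status exist anywhere. Secondary outcomes describes a subsample not limited to positives, and the Abstract calls it random. That inference fails, although the subsample remains secondary.

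The strongest defence is that the hypothesis section already promises a comparison of rates between groups, that an overall analysis and a mixed model are mentioned, and that the decisive model and time point may be fixed in an analysis plan not shown here. This has force: a missing detail would be no finding. But the article does write out an analysis for the primary outcome, and that analysis is split by baseline status. An analysis plan that followed it would inherit the mismatch.

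Splitting by baseline status does not itself bias the arm comparison, because baseline status is measured before randomisation. Nor does the label for people uninfected twice bias it: with no treatment effect, both arms have the same expected share. The label is a faulty interpretation, not a biased estimator.

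Finally, the small counts concern the infected stratum only, and they depend on the sample size used. Cluster randomisation describes 45 households with five members each, 225 per cluster, which conflicts with 80 and would give about 10 (4.6%) or 29 (13%) infected per village before loss.

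**Conclusion.** The point holds in this form: the description of the surveys and the primary analysis contradict each other, and under neither reading do the split models test the stated outcome. With redrawn samples they lack baseline values. With a cohort they estimate clearance and new infection separately, and the clearance model rests on about 3 to 8 people per village at 4.6% to 13% prevalence (0.6 to 11 over the stated range), while the trial was sized on 58 per village. The Discussion itself warns that prevalence may be low.

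These counts assume 58 completers per village, loss unrelated to infection, and study villages resembling the quoted prevalences. The contradiction and the mismatch with the outcome depend on none of these. It would go too far to conclude that the trial cannot test its hypothesis: the survey data support a direct comparison of prevalence under either design.

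**What to change.** 1. State once whether the 12, 24 and 30 month surveys redraw households or revisit the baseline participants, and align the Abstract, Study outcomes and measurements, Sample size calculation and Pre-post analysis with that statement.
2. Make the primary analysis one comparison of arms on infection status in everyone examined, whatever their baseline status, with a village effect and adjustment for baseline village prevalence. Add a person effect if people are revisited. The article already plans baseline adjustment by cluster mean for continuous outcomes; this extends the idea to the binary primary outcome. Name this comparison as the test of the null hypothesis.
3. Move the transition models to secondary analyses. Interpret uninfected-to-uninfected and infected-to-uninfected transitions only as contrasts between arms, and drop the reading of the former as preventive in itself.

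The cost is protocol and analysis-plan wording and some analysis work. Point 2 works under either design and needs no additional data. The transition results are kept but no longer carry the primary conclusion.
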